## Study outcomes

The main primary outcome in this study would be the evaluation of serum concentrations of high-sensitivity C-reactive protein (hs-CRP). We will also consider the assessment of other inflammatory factors, including tumor necrosis factor-α (TNF-α), interleukin 6 (IL-6), and anti-inflammatory factor interleukin-10 (IL-10) as well as the assessment of disease severity and disease-related disabilities lipid profile, anthropometric measures, dietary intake, and physical activity, which all would be considered as secondary outcomes.

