### Study sample size calculation

The required sample size was calculated based on the data from a previous study [27] considering a type I error of 5% (*α* = 0.05) and type II error of 20% (*β* = 0.20, power = 80%) and hs-CRP as the key variable. We considered the mean difference in serum hs-CRP levels of 5.71 between the two groups. Also, the average SDs reported for hs-CRP in the control and intervention groups were considered as 5.93. We used the suggested formula for parallel clinical trials and reached the sample size of 17 patients in each group.
$$ n=\frac{2\times {\left({Z}_{1-\frac{\alpha }{2}}+{Z}_{1-\beta}\right)}^2\times \mathrm{SD}2}{\mathrm{d}{}^2} $$$$ n=2\times {\left(1.96+0.85\right)}^2{(5.93)}^2/{(5.71)}^2=17 $$

Based on this formula and given a 20% drop-out in each group, we will need a sample size of 20 persons for each group.

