### Statistical analysis

Statistical analyses of all data will be performed using the SPSS software version 21.0 (SPSS Inc., Chicago, IL, USA). To handle non-adherence, we will use the intention-to-treat approach for data analysis. Missing values will be dealt with using the last observation carried forward (LOCF) method. Data will be expressed as mean ± standard deviations (± SD) and percentages. The one-sample Kolmogorov–Smirnov test will be used for assessing the normality of the distribution of data. In the case of a non-normal distribution of a variable, we will apply the log transformation. If the variables were non-normally distributed even after log transformation, we would use non-parametric tests in the analyses. Continuous variables will be compared between the two groups by independent samples *t*-test (or its non-parametric equivalent). We will apply the chi-square test to examine the distribution of participants in terms of categorical variables. To find the effect of the intervention on outcome variables, repeated measures analysis of variance (or its non-parametric equivalent) will be used. In these analyses, the effect of the intervention, time, and time-intervention interaction will be explored. The potential difference in baseline levels of outcome variables as well as differences in dietary intakes and physical activity levels, if any, between the two groups will be controlled for in these analyses. *P* values will be considered significant if they were < 0.05.

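### The analysis of hs-CRP names no deciding term in a two-time-point repeated-measures ANOVA and can be read as adjusting for baseline only when the groups differ

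*Protocol article*

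**What the plan says.** The Study outcomes section is clear on the endpoint: "The main primary outcome in this study would be the evaluation of serum concentrations of high-sensitivity C-reactive protein (hs-CRP"). Study design and intervention has the primary and secondary outcomes measured twice, at baseline and at the end of the 12 weeks.

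The Statistical analysis section uses repeated-measures analysis of variance, or a non-parametric equivalent, to find the effect of the intervention. In that model "the effect of the intervention, time, and time-intervention interaction will be explored". A single threshold of P < 0.05 covers all tests. No term is named as the one that decides the hs-CRP result.

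The same section lists what the model will adjust for when the arms are compared: "The potential difference in baseline levels of outcome variables as well as differences in dietary intakes and physical activity levels, if any".

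The sample size section works from a "mean difference in serum hs-CRP levels of 5.71 between the two groups" and says that the "average SDs reported for hs-CRP in the control and intervention groups were considered as 5.93". It does not say whether these are end-of-trial values or changes from baseline.

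**The concern.** With one measurement before treatment and one after, the three ANOVA terms answer different questions.

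- **Intervention main effect:** without baseline adjustment, it compares the arms on the average of the two measurements. Randomised arms have no expected difference at baseline, so it estimates half the treatment effect.
- **Time:** this is the before-after change pooled over both arms. It does not compare the arms.
- **Interaction:** this is the difference between arms in change from baseline. It is a treatment comparison, and unadjusted it is the same as a t-test on change scores.

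The term whose name sounds like the trial result is therefore the weakest of the two that compare the arms. If the deciding term is not fixed in advance, two tests can support a claim on hs-CRP. The covariate rule adds to this. Read as conditional, it lets the observed data choose the primary model, and it does so partly through diet and activity, which are recorded during the intervention, after randomisation.

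**Working it through.** **Inputs.** From the sample size section: difference d = 5.71, SD s = 5.93, two-sided alpha 0.05, power 80%, 17 per group before dropout and 20 after. The correlation r between baseline and week 12 is not in the document, so 0.3, 0.5 and 0.7 are assumed. The calculation also assumes equal SDs at both times, that 5.71 and 5.93 describe end-of-trial values, and no dropout.

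**The plan's own figure.** 2 × (1.96 + 0.85)² × 5.93² / 5.71² = 17.03, so the stated 17 reproduces. It is the size for one between-group comparison of means, and the section does not tie it to any of the three ANOVA terms.

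**Effect and SD behind each test, baseline not adjusted except in ANCOVA:**

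- Main effect: d/2 = 2.86, SD = s√((1 + r)/2)
- Interaction (change score): d = 5.71, SD = s√(2(1 − r))
- ANCOVA: d = 5.71, SD = s√(1 − r²)

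The variance of the interaction relative to ANCOVA is 2(1 − r)/(1 − r²) = 2/(1 + r). This exceeds 1 for every r below 1.

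**Worked case, r = 0.5, n = 20 per group, SE = SD × √(2/20):**

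- Main effect: SD 5.14, SE 1.62, ratio 2.86/1.62 = 1.76, power 40%
- Interaction: SD 5.93, SE 1.88, ratio 5.71/1.88 = 3.04, power 84%
- ANCOVA: SD 5.14, SE 1.62, ratio 5.71/1.62 = 3.52, power 93%

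**Power from the noncentral t distribution, r = 0.3 / 0.5 / 0.7:**

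| Test | 20 per group | 17 per group |
|---|---|---|
| Main effect, unadjusted | 45 / 40 / 36% | 39 / 35 / 31% |
| Interaction, unadjusted | 71 / 84 / 97% | 63 / 78 / 94% |
| ANCOVA, baseline always in | 87 / 93 / 99% | 81 / 88 / 97% |

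**Adjusting only on imbalance.** One possible reading of 'if any' is to use the unadjusted interaction unless baseline differs at P < 0.05. In a simulation of 4,000 trials per setting at 20 per group, this gave 72 / 84 / 97% power, against 86 / 91 / 98% for always-adjusted ANCOVA. The conditional rule therefore recovers almost none of the gain.

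**Two ways to succeed.** With equal SDs, the average and the change are uncorrelated. If either unadjusted test may count, the false-positive rate is 1 − 0.95² = 9.75%. Simulation at 17 and 20 per group gave 9 to 10%.

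**Baseline adjusted.** Write B for baseline and Y for week 12. Once B is a covariate, the responses (B + Y)/2 and Y − B differ from Y only by a scale factor and a multiple of B, which the covariate absorbs. The group and interaction tests then return the same P value as ANCOVA. The simulation confirmed this in every replicate.

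**The case against.** The strongest reply is that the text may already adjust for baseline. The qualifier 'if any' may belong only to diet and activity. No imbalance test or threshold is given, and some numerical baseline difference nearly always exists. On that reading the main-effect and interaction tests are both ANCOVA, and neither the power loss nor the doubled error rate arises. This stands: the wording permits the conditional reading but does not settle it.

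Second, even unadjusted, the interaction is an unbiased treatment comparison with the correct type I error. At 20 per group and a correlation of 0.5 it exceeds the planned 80%. If 5.71 and 5.93 are change values, it has the planned power by construction. This also stands. The loss is measured against ANCOVA and is not always a loss against the plan.

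Third, the choice of deciding term may be left to a statistical analysis plan that is not shown, and hs-CRP is already separated from the secondary outcomes. This stands in part. The article does commit to a model, a list of terms and a covariate rule, and those choices can be judged as written.

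A reader might also infer that all three effects, including time, are planned routes to an efficacy claim. The document does not support that. It says the effects will be explored, describes a parallel superiority trial and is sized on a between-group difference. Nothing presents the pooled time effect as efficacy, so error rates that count it do not belong here.

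**Conclusion.** The point holds in a limited form. The article leaves open which term decides hs-CRP and words its covariate rule so that it can be read as data-dependent. The consequences belong to the branch in which baseline is not adjusted. There the main effect has 36 to 45% power at 20 per group, the interaction gives up between 2 and 16 percentage points to ANCOVA (97 against 99% and 71 against 87%), and accepting either term roughly doubles the 5% error rate. These figures rest on assumed correlations of 0.3 to 0.7, equal SDs, no dropout, the untransformed scale, and 5.71 and 5.93 being end-of-trial values. It would go too far to say that the unadjusted branch is certain or usual, or that the main effect has been chosen as decisive; the document says neither. The matter should be fixed, but it does not invalidate the planned analysis, because an unbiased test is among the terms listed.

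**What to change.** Before unblinding, name one primary test: an ANCOVA of week-12 hs-CRP on treatment arm with baseline hs-CRP always included, on the log scale if the plan's transformation applies. Report the adjusted difference, its 95% confidence interval and P value. Use the same model for each secondary outcome, with that outcome's own baseline.

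State that the group main effect and the time effect from a repeated-measures model will not be used as evidence of efficacy. State also that observed differences in baseline, or in diet and activity recorded after randomisation, will not decide the covariates of the primary model. Say whether 5.71 and 5.93 are end-of-trial values or changes, so that the sample size can be matched to the named test.

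The cost is a change of analysis wording. Baseline hs-CRP is already being collected, and neither the sample size nor the visit schedule is affected.

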### Study design and intervention

The diagram for Standard Protocol Items: Recommendations for Interventional Trials (SPIRIT) is shown in Fig. 2. After recruiting participants, they will be stratified based on age (20 to < 40 and 40–60 years), BMI (< 30 and ≥ 30 kg/m^2^), and type of medicines (nonsteroidal anti-inflammatory drugs (NSAIDs)/disease-modifying antirheumatic drugs (DMARDs)/steroids/immunosuppressive) into different blocks and then will be randomly allocated to the intervention or control groups. For each patient in a particular block, a matched person in terms of the abovementioned variables would be placed in that block. Then, these two patients in a given block would be randomly assigned to the intervention and control groups. To do randomization, an identification code will be given to each eligible patient in each block, and then, the code of patients with the same age, BMI, and medication will be stated in the lottery container. A person who will be unaware of the study aims will be asked to draw the codes out of the container randomly. The first code will be assigned to the intervention group and the second code to the control group. This will be done for all containers. All patients, researchers, rheumatologists, statistical analysts, and laboratory staff will be blind to the intervention. Random allocation will be done by a third person who is unaware of the aim of our study. Patients in the intervention group (*n* = 20) will receive 30 g/day low-salt and low-fat probiotic cheese. Participants in the control group (*n* = 20) will receive low-salt and low-fat cheese without probiotics. Packaging of both kinds of cheeses would be in the same shape and color. The intervention will last for 12 weeks. Assessment of primary and secondary outcome variables will be done at the study baseline and end of the trial. A standard container will be given to participants, and they will be asked to that container to make sure they are consuming the specified amount. Participants will be asked not to change their lifestyle, dietary habits, and medicines throughout the study. To assess dietary intakes throughout the study, we will fill four 1-day 24-h dietary recalls (including two working days and two non-working days) once every 3 weeks by telephone interview. To complete dietary recalls, participants will be asked to report dietary intakes based on household measures. Then, we will convert the reported amounts to grams using available booklets. The average dietary intakes in these 3 days will be considered as participants’ mean dietary intakes throughout the intervention. To obtain nutrient intakes based on these food recalls, we will use the Nutritionist IV software (based on US National Nutrient Databank) modified for Iranian foods. In addition, four 1-day physical activity records (including two working days and two holidays) will be completed from all patients at weeks 3, 6, 9, and 12 of intervention to assess physical activity during the study. Participants will be requested to report all activities they have during a specific day with the name and type of activity as well as the time spent. All participants will be educated on how to record their activities throughout the study before the start of the trial. Furthermore, patients in both groups will be asked not to change their physical activity throughout the trial.

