### Assessment of dietary intake and physical activity

To ensure adherence to the intervention and avoid changes in dietary intakes throughout the study, assessment of dietary intake will be done using four dietary records throughout the study, one in every 3 weeks. Participants will be trained at the study baseline on how to record their dietary intakes. Days of dietary recording will be determined by investigators, such that two weekdays and two weekend days will be included in these recordings. Subjects will be requested not to change their usual dietary intakes on the day of recording their intakes. All records will be reviewed immediately, and possible problems will be resolved by interview. To compute nutrient intakes of study participants based on the analysis of these dietary records, we will use the Nutritionist IV software, in which the original database is based on the United States Department of Agriculture (USDA) food composition table; however, a modification will be done for the Iranian local foods.

To ensure a lack of difference in activity levels between intervention and non-intervention groups throughout the study, physical activity will be assessed by asking study participants to record their usual activities on specific days. The number of physical activity records will also be four, including two weekdays and two weekends. All the records will be taken once in 2 weeks. Therefore, all patients will complete four dietary records and four physical activity records during the study. Data from physical activity records will be processed using MET-h/day values given for each physical activity based on published guidelines [26].

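### The efficacy model conditions on on-treatment diet and physical activity whenever the arms differ, so the estimate may not be the randomised effect; direction and size of the bias are unknown

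*Protocol article*

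**What the plan says.** All references are to the protocol article.

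- **Model (Statistical analysis).** "To find the effect of the intervention on outcome variables, repeated measures analysis of variance (or its non-parametric equivalent) will be used". Arm, time and their interaction are examined.
- **Covariates (same section).** Besides baseline differences in the outcome, the plan says "as well as differences in dietary intakes and physical activity levels, if any, between the two groups will be controlled for in these analyses". It gives no test or threshold for deciding that a difference exists.
- **Diet (Study design and intervention).** Four recalls are taken, "once every 3 weeks by telephone interview". Their average is used as the "mean dietary intakes throughout the intervention".
- **Activity (same section).** Four records are completed "at weeks 3, 6, 9, and 12 of intervention to assess physical activity during the study".
- **Status (Study outcomes).** The list of secondary outcomes ends with "anthropometric measures, dietary intake, and physical activity, which all would be considered as secondary outcomes".
- **Baseline.** Study design and intervention says in general terms that primary and secondary outcomes are assessed at baseline and at the end. Neither that section nor Assessment of dietary intake and physical activity describes a baseline diet or activity value, or says that one would serve as the covariate.

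**The concern.** A randomised comparison is protected from confounding because arm is independent of everything fixed before allocation. Diet and activity measured during the 12 weeks lack that protection. A patient whose disease eases may move more or eat differently, so an arm difference in these variables may itself be an effect of treatment.

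Conditioning on them then does two things. It removes any part of the hs-CRP effect that runs through them. It also links arm to any unmeasured cause that they share with hs-CRP.

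The *if any* condition adds to this. The model is settled after looking at on-treatment data, and the adjustment enters when the arms differ, which is when it can do harm. The primary estimate, its power and its type I error are all exposed.

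**Working it through.** **1. The plan's own figure.** The sample size section uses a difference of 5.71, an SD of 5.93, two-sided α = 0.05 and 80% power:

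n = 2 × (1.96 + 0.85)² × 5.93² / 5.71² = 2 × 7.896 × 35.165 / 32.604 = 17.03, stated as 17 per arm.

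This reproduces. With 20 analysed per arm, power is 86%. The standardised effect is 5.71 / 5.93 = 0.963 SD. The plan gives no figure for diet or activity, so everything in steps 2 to 4 rests on assumed values.

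**2. Common cause, no mediation.** Let g be arm, M the on-treatment covariate, U an unmeasured cause of both M and hs-CRP, and a the shift in M caused by treatment. M and Y have unit within-arm SD.

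- M = a·g + √0.5·U + noise
- Y = −0.963·g + λ·U + noise, with λ = −0.5 or +0.5

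The within-arm slope of Y on M is λ√0.5 = ±0.354. The adjusted arm coefficient is therefore −0.963 − a·λ√0.5:

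| Shift a | λ = −0.5 | λ = +0.5 | Bias when adjusted |
|---|---|---|---|
| 0 | −0.963 | −0.963 | nil |
| 0.2 | −0.892 | −1.034 | 0.071/0.963 = 7% |
| 0.5 | −0.786 | −1.140 | 0.177/0.963 = 18% |
| 0.8 | −0.680 | −1.246 | 0.283/0.963 = 29% |

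Simulation with 20 per arm agrees at the 0.5 and 0.8 SD shifts: 0.79 and 0.68 SD for λ = −0.5, and 1.13–1.14 and 1.25 SD for λ = +0.5. The sign of the bias depends only on the sign chosen for λ.

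**3. The same model under the conditional rule.** The last column of that table is the bias when the adjusted model is used. The plan uses it only if the arms differ, read here as p < 0.05 on a t-test of M. Averaged over all simulated trials:

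| Shift a | Rule triggers | Bias, either direction | On 5.71 |
|---|---|---|---|
| 0 | about 5% | nil | 5.71 |
| 0.2 | – | 2–3% | ±0.1 to 0.2 |
| 0.5 | 35% | 10% | ±0.6 |
| 0.8 | 69% | 24–25% | ±1.4 |

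At a = 0.5 the average exceeds 35% × 18% = 6%. The trials that escape adjustment are those where M happened to differ little, and their unadjusted estimates are selected in the same direction. Where the bias shrinks the effect, power falls from about 85% to 76% (a = 0.5) and 59% (a = 0.8). With no true effect and a = 0.8, type I error is about 11%.

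**4. Mediation and a second common-cause setting.** A separate simulation keeps the total effect at −5.71 and lets part of it run through M. Estimates and power are under the conditional rule, and power is compared with the unadjusted model:

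| Share mediated | Shift | Mean estimate | Power, unadjusted → rule |
|---|---|---|---|
| 20% | 0.5 SD | −5.06 | 79% → 68% |
| 20% | 1 SD | −4.66 | 84% → 57% |
| 40% | 0.5 SD | −4.3 | 64% → 46% |
| 40% | 1 SD | −3.5 | 79% → 37% |

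Always adjusting removes the mediated share: 0.8 × 5.71 = 4.57 and 0.6 × 5.71 = 3.43. With nothing mediated and a common cause loading +0.5 on both variables, the rule instead inflates the estimate to −6.1 (0.5 SD) or −7.1 (1 SD). With no true effect and a 1 SD shift, type I error is about 10%. With no shift in M, the estimate stays at about −5.7.

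All these runs compare a single outcome value per patient instead of fitting the full repeated measures model.

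**The case against.** The strongest reply is that a shift is unlikely. Both arms eat low-salt, low-fat cheese, the trial is double-blind, and patients are told to keep diet and activity unchanged. With no shift there is no bias, and at 0.2 SD it is only 2–3%. This stands as a limit on size. It does not rescue the rule, which is written for the case where a difference does appear.

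Three stronger readings are tempting, and the document supports none of them:

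- *Diet and activity have no baseline record.* The general statement that secondary outcomes are assessed at baseline covers them, and the SPIRIT chart is not available here. What can be said is that the measurements described in detail are on treatment, and that the diet value is defined as the mean over the intervention.
- *The adjustment shrinks the effect.* It may. Steps 2 and 4 show that it can equally inflate the effect, and the document does not settle the sign.
- *The conflicting measurement schedules strengthen the argument.* They are real but separate. They make the covariate hard to reproduce and say nothing about bias.

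The p < 0.05 trigger is likewise an assumption, since the plan leaves *if any* undefined. Adjusting for the baseline outcome value is sound and is not challenged, except that it should not be conditional.

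**Conclusion.** The concern holds in this form: the plan conditions the efficacy estimate, including that for hs-CRP, on variables that it measures during treatment and itself lists as outcomes, and it does so when an arm difference is observed. The estimate then ceases to be the randomised effect whenever treatment shifts diet or activity.

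The size of the bias cannot be derived from the document. In the common-cause illustration it runs from nil with no shift to about a quarter of the effect at 0.8 SD, in either direction. These figures rest on the assumed shifts, the ±0.5 loading and the p < 0.05 trigger. The case for changing the plan is therefore one of principle, with a possible effect on the primary result, and not a demonstrated bias of known size.

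**What to change.** 1. Remove on-treatment dietary intake and physical activity from the primary efficacy model for hs-CRP, and likewise from the models for the other outcomes.
2. Adjust unconditionally, and only for pre-randomisation variables fixed in advance: the baseline value of the outcome and the randomisation factors (age, BMI and medication type).
3. Report diet and activity by arm as the secondary outcomes they are. Label any model that includes them exploratory, and do not let an observed difference decide whether the primary model changes.

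The cost is wording only. The planned 17 per arm before drop-out, and 20 after it, do not change.

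Separately, and minor: reconcile the four recalls with "The average dietary intakes in these 3 days will be considered as participants’ mean dietary intakes throughout the intervention", and reconcile the activity records at weeks 3, 6, 9 and 12 with the statement under Assessment of dietary intake and physical activity that "All the records will be taken once in 2 weeks".
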